## Assignment of interventions: allocation

### Sequence generation {16a}

The unit of randomization will be the community. A total of 10 communities (five from each LGA) will be randomly selected from the list of communities from a ward obtained from the Local Government secretariat. The selected communities from each LGA will be grouped into two non-contiguous groups based on geographical distance between communities. One group will be randomly assigned to intervention and another to control. This will ensure that intervention communities are closed together but at far distance from control communities to minimize contamination. The final randomization of intervention and control communities will be done by a statistician who is not involved in the implementation of field activities. Assignment of communities to either the intervention or control arm will be done after the baseline survey. Given the nature of the intervention, it is not possible to blind the CORPs who will be involved in the delivery of the intervention.

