## Methods: participants, interventions and outcomes

### Study setting {9}

The study will be conducted in three states selected from the six geopolitical zones in Nigeria comprising of Abia (South East), Kano (North West) and Oyo (South West) states. A state in Nigeria comprises a number of LGAs and each LGA is made up of 10 to 12 wards.

Two Local Government Areas (LGAs) (one urban and one rural) each were selected from each state based on participation in past hypertension survey and good cooperation received from the community members in past studies. Thus, in Abia State—Umuahia North (urban) and Isuikwuato (rural) with population of 292,300 and 151,700; in Kano state—Tarauni (Urban) and Bichi (Rural) with population of 387,100 and 308,600; and in Oyo state—Ibadan North (Urban) and Ona-Ara (Rural) with population of 473,900 and 373,100 respectively will be studied [31]. Figure 2 is the map of Nigeria showing selected states visited.

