**Fig. 2 Fig2:**
[figure not shown]
Map of Nigeria showing the states selected for study

In the urban sites, the predominant economic activities are white- and blue-collar jobs, trading and other commercial activities. There are small-, medium- and large-scale industries and very little farming activities, whereas, in the rural sites, the people are predominantly farmers with few small-scale industries and trading.

The Local Government in each of the states has a Secondary/Comprehensive health facility, while each ward has a primary health facility (PHC). The PHCs are manned by a team of medical officer, nurses, community health extension workers, junior community health extension workers and pharmacy assistants headed by the medical officer or senior nurse where there is no medical officer.

Existing within the wards are trained lay persons who have served as community health workers at some point or participated in previous community-based studies such as the home management of malaria using artemisinin-based combination therapy study. Some will be selected from them to serve as CORPs. Where there are no CORPs, communities shall nominate persons who meet selection criteria to represent their communities.

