### Intervention description {11a}

The highlights of the activities and assessments for intervention and control arm are shown in Table 1. The components of the intervention include the following.

**Table 1 Tab1:** Highlights of the activities and assessments for intervention and control arm

	Activity	Intervention	Control
1	Baseline survey	Yes	Yes
2	Selection, screening and standard training of CORPs on blood pressure screening	Yes	Yes
3	Training on additional information on follow-up care for hypertensive patients and CORPs coordination	Yes	No
4	Trained CORPs screen and refer community members found to have high blood pressure	Yes Referral to the designated primary healthcare centre in the community	Yes Referral will be to the community member’s health facility of choice
5	Train health facility staff in designated primary healthcare facilities on the National guideline for hypertension treatment	Yes	No
6	CORPs Monthly checking and recording of blood pressure as well as providing health education/counselling support by the CORPs	Yes	No
7	SMS messaging on medication and healthy lifestyle adherence to support follow-up care	Yes	No
8	Anthropometry measurement, e.g. weight, height and body mass index (BMI) Biochemical measurement ECG	Yes	No
9	Endline survey	Yes	Yes

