### Recruitment {15}

Persons found to be hypertensive during baseline survey will be noted and contact address taken including the phone contact. Subsequently, they will be invited to the primary health facility in their neighbourhood for recruitment into the study (Intervention arm). In addition, the trained CORPs will screen and refer community members found to have high blood pressure to the primary healthcare facilities in the community (intervention arm) or health facility of their choice (control arm). The CORPs will carry out sensitization campaign in the community through visits to community stakeholders including the community chiefs, heads of religious bodies, leaders of artisans, head of community structures such as Chairman of Landlord Associations, and talks in churches, mosques and community meetings to intimate them of the programme and conduct blood pressure screening. The CORPs shall be provided with identification poster for display in front of their houses to indicate that blood pressure screening service is available. If the required number of hypertensive patients to be recruited in a community is not achieved, the neighbouring community may be co-opted and the CORP mobilized to cover the community as well. At the health facility, patients presenting with other ailments or walk-in patients or self-referred patients who present at the health facilities found to be hypertensive shall be requested to participate in the study. The physician/healthcare worker will confirm diagnosis and commence antihypertensive medications.

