### Implementation {16c}

This is a cluster-randomized trial. Clusters or communities will be randomized and not individual participants. Allocation will be done by the statistician while participants will be enrolled by CORPS and health workers at the primary health centres.

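### Staff training acts through the primary health centre, but the arms are separated only by geography, so control patients can reach trained staff and the effect can be diluted by an unknown amount

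*Protocol article*

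**What the plan says.** All references are to the protocol article.

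- **Unit and sampling (Sequence generation {16a}).** "The unit of randomization will be the community". Ten communities per state, five from each local government area (LGA), "will be randomly selected from the list of communities from a ward obtained from the Local Government secretariat".
- **Forming the arms (same section).** "The selected communities from each LGA will be grouped into two non-contiguous groups based on geographical distance between communities". One group is then randomised to intervention and the other to control. The stated purpose is to minimise contamination. The Discussion adds buffer zones between the groups.
- **Wards and facilities (Study setting {9}).** "each LGA is made up of 10 to 12 wards", and "each ward has a primary health facility (PHC").
- **The facility component (Intervention description {11a}, Table 1, row 5).** "Train health facility staff in designated primary healthcare facilities on the National guideline for hypertension treatment": yes for intervention, no for control.
- **Where patients go (Table 1, row 4, and Recruitment {15}).** Intervention patients are referred to the designated PHC. Control patients are referred to the "health facility of their choice (control arm").
- **Shortfall rule (Recruitment {15}).** If a community yields too few patients, a neighbouring one may be added. No condition is set on distance or facility.

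**The concern.** Most of the package follows the patient's residence: home visits by the community-oriented resource persons (CORPs), group sessions and messages. Staff training does not. It follows the clinic, and anyone treated there can benefit from it. The grouping rule keeps residents of the two arms apart but is silent on which clinic serves which group, and free choice of facility leaves a trained PHC open to control patients.

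A control patient treated by trained staff receives part of the intervention. This pulls the estimated difference in blood pressure control towards zero, for a primary outcome planned on a 30-point contrast. Unless the facility attended is recorded for control patients, the extent cannot be judged afterwards.

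**Working it through.** **Step 1. Can a trained PHC serve control patients?** There are two readings of the sampling sentence.

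- *One ward per LGA.* All five communities lie in one ward. If that ward's PHC is its only one, it serves both groups.
- *Several wards per LGA.* The groups may have different PHCs, but a control patient may still choose a trained one.

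The answer is yes under either reading. The reading changes only how likely it is.

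**Step 2. Size of the dilution.** Inputs from Sample size {14}: control rate 30%, intervention rate 60%, difference 30 points. Two inputs are not in the document and are assumed:

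- f, the share of control patients treated at a trained PHC;
- s, the share of the 30-point effect carried by the facility.

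With the intervention rate held at 60%:

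control rate = 30 + f × s × 30; difference = 60 − control rate.

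For s = 0.5 and f = 0.2: 30 + 0.2 × 0.5 × 30 = 33, difference 27 points. For s = 0.5 and f = 0.5: 30 + 0.5 × 0.5 × 30 = 37.5, difference 22.5 points, a quarter below plan.

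**Step 3. What this does to power.** The plan's own figure is 50 per arm in each LGA after 10% attrition. It does not reproduce: two-sided 5% and 90% power with pooled variance give 56, or 56/0.9 = 63 with attrition. That is a separate matter. I take the planned numbers as they stand: 50 × 0.9 = 45 evaluable per arm in one LGA, and 6 × 45 = 270 per arm overall.

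Power = Φ{[d√n − 1.96√(2p̄(1 − p̄))] / √(p₁(1 − p₁) + p₂(1 − p₂))}, where d is the difference and p̄ the mean of the two rates. Clustering is ignored.

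| s | f | Control rate (%) | Difference (points) | Power, 45 per arm | Power, 270 per arm |
|---|---|---|---|---|---|
| any | 0 | 30 | 30 | 83% | >99% |
| 0.25 | 0.5 | 33.75 | 26.25 | 71% | >99% |
| 0.5 | 0.2 | 33 | 27 | 74% | >99% |
| 0.5 | 0.5 | 37.5 | 22.5 | 57% | >99% |
| 0.5 | 1 | 45 | 15 | 29% | 94% |
| 1 | 0.5 | 45 | 15 | 29% | 94% |

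To allow for clustering I assume 18 patients per community (270/15) and an intracluster correlation of 0.02 to 0.10, neither of which is in the document. The design effect is 1 + 17 × ICC, or 1.34 to 2.70. Pooled power is then above 99% down to about 90% at 22.5 points, and 86% down to 57% at 15 points.

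**The case against.** Much can be said for the plan, and part of it stands.

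- **A shared PHC is not established.** A reader might infer that both arms are served by one PHC. The setting section says each ward has a facility, not only one. Table 1, the screening section and Recruitment {15} place the intervention facility in the community or neighbourhood, and the retention section {18b} recruits from the clinic's catchment. The sampling sentence is also loose: taken literally, one ward would have to span two LGAs. Far-apart groups with a buffer are hard to form inside one of 10 to 12 wards. This stands: a shared PHC is possible, not shown.
- **Distance gives some protection.** If clinics serve their neighbourhoods, separating residents also makes cross-use of clinics less likely. A reader might infer that the contamination safeguard fails altogether. The text does not support that. It is partial for this component, and the plan claims only to minimise or reduce contamination.
- **Enrolment is separated by arm.** "participants will be enrolled by CORPS and health workers at the primary health centres" (Implementation {16c}) draws no distinction, but Recruitment {15} does. I place no weight on the shorter line.
- **Free choice is the comparator.** Usual care is defined that way, in a real-life setting. That is a fair reason to leave the choice alone, but not to leave it unrecorded.
- **Only part of the package can leak.** The guideline is already recommended nationally for primary facilities, so only the added effect of training crosses over. Home visits and messages stay in the intervention arm.

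What the objection does not answer is that no rule links the grouping, or the choice of PHCs for training, to the clinics serving control communities.

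**Conclusion.** The point holds in a limited form. A component intended for one arm is delivered at facility level. The groups are formed on distance alone, may come from the same ward, and control patients may attend a trained PHC. The difference **can** be diluted towards no effect. The documents do not show that it **will** be, or by how much.

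With half of the effect assumed to come from the facility, the difference is 27 points at 20% cross-use, 22.5 at 50% and 15 at 100%. These figures rest wholly on the assumed f and s.

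It would also go too far to infer that the pooled trial loses its power. At 22.5 points, power with 270 evaluable per arm stays above 99% ignoring clustering, and is about 90% at the highest intracluster correlation assumed. The low figures for a single LGA partly reflect its size, since power there is 83% with no dilution. The main harm is an underestimated effect whose size nobody could later assess. The bias runs against the intervention, so this mechanism would not produce a false claim of benefit.

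**What to change.** 1. **Sequence generation {16a}:** add PHC catchment to the distance criterion when the two groups in each LGA are formed, so that no PHC designated for training has a control community in its catchment, where the selected communities allow it.
2. **Recruitment {15}:** apply the same condition to any co-opted neighbouring community.
3. **Sequence generation {16a}:** reconcile the reference to a ward with the number of wards actually used in each LGA.
4. **Data collection:** record on the existing forms the facility each control patient attends, and report the share treated at a trained PHC.

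Do not redraw wards or replace communities already surveyed. Allocation follows the baseline survey, and Trial status reports the formative phase as concluded, so new sampling would probably mean a new baseline survey.

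The cost is fewer possible groupings per LGA and one extra data item. Trial status says that recruitment for the intervention has not started, but not whether allocation or staff training has been done. If the groups are already fixed, item 1 may no longer be open. Items 2 to 4 remain available.

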**Methods:**

An intervention study will be conducted in three states using a mixed method design. First is a baseline survey using a semi-structured pre-tested questionnaire to collect information on demographics, clinical data, knowledge, occurrence and risk factors of hypertension among 1704 adults ≥18 years. Focus group discussions (FGD) and key informant interviews (KII) will be conducted to explore a community’s experience of hypertension, challenges with hypertension management and support required to improve control in 10 selected communities in each state. The second is a cluster-randomized controlled trial to evaluate effect of a package on reduction of blood pressure (BP) and prevention of cardiovascular (CVD) risk factors among 200 hypertensive patients to be followed up in intervention and control arms over a 6-month period in each state. The package will include trained CORPs conducting community-based screening of BP and referral, diagnosis confirmation and initial treatment in the health facility, followed by monthly home-based follow-up care and provision of health education on hypertension control and healthy lifestyle enhanced by phone voice message reminders. In the control arm, the usual care (diagnosis, treatment and follow-up care in hospital of a patient’s choice) will continue. Third, an endline survey will be conducted in both intervention and control communities to evaluate changes in mean BP, control, knowledge and proportion of other CVD risk factors. In addition, FGD and KII will be used to assess participants’ perceived quality and acceptability of the interventions as delivered by CORPs.

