The population characteristics of the urban and rural areas could differ especially with age and sex bearing in mind population migration factors and dynamics. This may distort the true effect of the intervention on outcome as CVD risk factors varies in these groups of people. This will be adjusted at analysis using multilevel analysis with random effect model. Bias in the intervention study will be minimized by randomization. The possible contamination between control and intervention arm will be reduced by grouping/clustering the communities before randomization and ensuring buffer zones exist between them to limit diffusion.

Cluster-randomized design is appropriate for this study which by nature is evaluating the effectiveness of an interventions in a “real-world setting” [48], and meant to provide health education at both community and individual levels. In addition is the fact that it is also an effective way to avoid contamination. The limitations associated with its use such as prevention of interference shall be giving much attention at analysis.

In conclusion, this study stands to provide evidence-based information for scaling up task sharing as well as community-clinical linkage in the control of hypertension in Nigeria. It is expected that this intervention will bring about early detection of hypertension, reduction in mean blood pressure and an increase in the proportion of patients with controlled blood pressure. In addition, we expect an improvement in the mean quality of life score; healthy lifestyle and competent CORPs as well as the reduced mean cost of treatment of hypertension in the intervention arm of the study. All of these will inform policy review to guide the control of hypertension and reduction in cardiovascular diseases risk in Nigeria.

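### The unit actually allocated is one of two geographic groups of communities per LGA (12 groups in 6 pairs), not the community as declared, and the between-arm analysis should be defined at group level

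*Protocol article*

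**What the plan says.** Sequence generation {16a} opens with the declaration "The unit of randomization will be the community". On selection it says "A total of 10 communities (five from each LGA) will be randomly selected", and the Abstract confirms "10 selected communities in each state". Study setting {9} adds "Two Local Government Areas (LGAs) (one urban and one rural) each were selected from each state", in three states.

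Sequence generation {16a} then describes the allocation: "The selected communities from each LGA will be grouped into two non-contiguous groups based on geographical distance between communities", followed by "One group will be randomly assigned to intervention and another to control". The stated aim is to keep intervention communities near each other and far from control communities. The Discussion confirms the order of events: "The possible contamination between control and intervention arm will be reduced by grouping/clustering the communities before randomization".

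Concealment mechanism {16b} and Implementation {16c} again describe communities as the clusters that are randomised.

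For analysis, Statistical methods {20a} plans a random-effect logit model for the between-arm effect. The Discussion, writing about urban and rural population differences, says "This will be adjusted at analysis using multilevel analysis with random effect model". Neither place gives the level of the random effect or mentions the geographic group.

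**The concern.** The declaration and the procedure disagree. All communities in a group receive their arm from the same draw, so the group is what chance allocates.

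This matters because the groups are formed by proximity. Neighbouring communities may resemble each other in environment and access to care. In the intervention arm they may also share a designated primary healthcare centre and its trained staff. Any such shared component is common to every community in the group and does not average out over communities.

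A model with the community as the cluster would count about 15 independent units per arm where there are 6. If the groups within an LGA differ, the primary comparison would then have too small a standard error and too many degrees of freedom, and a false-positive rate above 5%.

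**Working it through.** **Counting the units.**
- Communities: 5 per LGA × 2 LGAs × 3 states = 30.
- LGAs: 2 × 3 = 6, hence 6 draws.
- Groups: 6 × 2 = 12, in 6 pairs. Five communities cannot split evenly, so 3 and 2 is assumed.
- Patients: 50 per arm per LGA × 2 arms × 6 LGAs = 600, which matches Sample size {14}. That section uses no ICC or design effect. With 10% attrition, 50 × 0.9 = 45 are evaluable per group.

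**Standard error.** Set the total variance to 1, with group ICC ρg and community ICC ρc, both assumed. There are on average 2.5 communities per group and 15 per arm.
- True variance of an arm mean: [ρg + ρc/2.5 + (1 − ρg − ρc)/50] / 6
- Variance as seen with communities treated as independent: (ρg + ρc)/15 + (1 − ρg − ρc)/300

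Example with ρg = ρc = 0.02:
- True: (0.02 + 0.008 + 0.0192)/6 = 0.00787
- Community-level: 0.00267 + 0.0032 = 0.00587
- SE ratio: √(0.00787/0.00587) = 1.16

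**Type I error.** Simulation under no effect (6 LGAs, groups of 3 and 2, 50 patients per group, 6,000 runs, linear approximation, nominal 5%):

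| ρg | ρc | True SE / community-level SE | Community level, LGA fixed, t with 23 df | LGA-paired groups, t with 5 df |
|---|---|---|---|---|
| 0 | 0.02 | 1.00 | 4.3% | 4.7% |
| 0 | 0.05 | 1.00 | 4.4% | 5.0% |
| 0.01 | 0.02 | 1.09 | 6.6% | 4.5% |
| 0.02 | 0.02 | 1.16 | 9.4% | 4.7% |
| 0.02 | 0.05 | 1.12 | 8.9% | 5.4% |
| 0.05 | 0.02 | 1.28 | 14.8% | 4.8% |
| 0.05 | 0.05 | 1.23 | 13.3% | 5.3% |

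A second simulation used a binary outcome at 30%, 45 evaluable per group and ρc = 0.02. At ρg = 0.01, 0.02 and 0.05, the community-level t test rejected in 6.9%, 9.5% and 14.5% of runs. The z test rejected in 8.5%, 11.5% and 16.8%. At ρg = 0 the figures were 4.9% (t) and 5.8% (z).

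**Critical values.** The two-sided 5% point is 2.07 with 23 df and 2.57 with 5 df.

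**Power of the paired group-level test** for 30% against 60%, 45 evaluable per group, assuming the same effect in every LGA. The variance of a pair difference is V = (0.3 × 0.7 + 0.6 × 0.4) × [ρg + ρc/2.5 + (1 − ρg − ρc)/45], and the noncentrality is 0.30/√(V/6).
- ρg = 0.01, ρc = 0.02: V = 0.45 × 0.0396 = 0.0178; noncentrality 5.51; power about 99%.
- ρg = 0.05, ρc = 0.02: V = 0.45 × 0.0787 = 0.0354; noncentrality 3.91; power about 87%.
- ρg = 0.05, ρc = 0.05: V = 0.45 × 0.09 = 0.0405; noncentrality 3.65; power about 83%.

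**Permutation test.** There are 2^6 = 64 possible allocations. The smallest two-sided p-values are 2/64 = 0.031 and 4/64 = 0.0625.

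**The case against.** The strongest reply is that the article never specifies a community-level model. A multilevel model could place communities within groups within LGAs, and an analysis plan that is not shown may do so. This stands. A reader might infer that the planned p-values will be too favourable, but the documents support that only conditionally: it follows if the analyst takes the declared cluster as the level of the random effect.

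The size is also uncertain. Every ICC is an assumption. Control patients attend a facility of their choice, so a control group need not share a provider. Sequence generation {16a} speaks of communities listed from a ward, which could make the two groups of an LGA alike. Both points allow a small group ICC, but neither gives reason to set it at zero.

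Two stronger readings should be set aside. A reader might infer that the plan relies on a large-sample Wald test, but the article names no reference distribution. A reader might also infer from the Discussion that age and sex are to be handled by a random effect alone. Statistical methods {20a} foresees identifying baseline variables that need adjustment, so the Discussion sentence is loose wording and not a defect in the plan.

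Leaving the matter to an analysis plan does not remove the core point. The article states two different units within one section and repeats the wrong one in the next two, so a plan that adopts its cluster definition inherits the error.

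**Conclusion.** The declared unit is wrong as written. On the described procedure, 12 groups in 6 LGA pairs are allocated by 6 draws. This part rests only on the document's own text and simple counting.

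The effect on the analysis is conditional. If the community is used as the cluster, and under the assumed group ICCs of 0.01 to 0.05 and community ICCs of 0.02 to 0.05, type I error is about 6% to 15% with a t reference and up to about 17% with a z test. With no variation between groups within an LGA, there is little or no inflation. The direction is secure for any positive group ICC; the amount is not known. The paired group-level comparison holds about 5% in every scenario examined.

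**What to change.** Correct Sequence generation {16a}, Concealment mechanism {16b} and Implementation {16c} to say that the allocated unit is the geographic group of communities within an LGA, with one draw per LGA, and give the resulting number of groups.

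Define the primary between-arm analysis at that level: LGA as stratum (fixed effect), the group as cluster and community nested within it. Pre-specify one small-sample reference, for example the LGA-paired group-level comparison with 5 degrees of freedom. A permutation test over the 64 allocations can serve as a sensitivity analysis. State in advance that it reaches 5% only if all six LGAs favour the same arm.

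This changes wording and analysis only; field procedures stay the same. The price is few degrees of freedom and wider intervals. By the approximation above, power for 30% against 60% is about 83% to 99% under the assumed ICCs. It meets the planned 90% at group ICCs up to 0.02 and falls below it at 0.05.
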